#### **4.4 Subject Screening**

##### **4.4.1 Enrollment Procedure**

The investigator will enroll subjects as follows:

1. Obtain informed consent signed by the subject or the subject's legally acceptable representative prior to any study-related procedures.
2. Subject eligibility will be formally determined by the Principal Investigator or appropriately trained designee after reviewing the inclusion/exclusion criteria.

Subjects who do not meet the relevant criteria for this study (screen failures) may be rescreened. If a subject is to be considered for re-screening, the investigator must contact the sponsor medical monitor. Each subject may be rescreened once. At the time of rescreening, the subject's legally acceptable representative must re-sign the Informed Consent Form (ICF) and will be reassigned with a screening number.

#### 4.4.2 Handling Procedures for Incorrectly Enrolled Subjects

The inclusion criteria must be strictly followed. If a subject is found to be enrolled that does not meet the eligibility criteria, the sponsor's medical monitor and the investigator will discuss whether to continue the subject in the study.

#### 4.4.3 Randomization and Blinding

"This was a multicenter, randomized, double-blind (subject, investigator), placebo-controlled study, as described in Section 8.6."

#### 4.5 Subject Replacement, Discontinuation, and Withdrawal Criteria

##### 4.5.1 Subject Replacement

Subjects who are not dosed after randomization will be replaced, unblinded and assigned a randomization number offline by the sponsor's unblinded statistician.

##### 4.5.2 Discontinued medication

If a subject experiences any of the following conditions during the study, the investigator should consider discontinuing study drug after discussion with the sponsor:

- 1) Marked increase from baseline in liver enzymes as defined in any of the following Table 13:

Table 13. Liver Enzyme Elevations at Baseline and during the Treatment Period

| Baseline                        | Treatment Period                                                                                                |
|---------------------------------|-----------------------------------------------------------------------------------------------------------------|
| ALT/AST < 1.5 x ULN             | ALT Or AST $\geq$ 5 Times ULN                                                                                   |
|                                 | ALT or AST $\geq$ 4 times ULN for more than 2 weeks                                                             |
|                                 | ALT or AST $\geq$ 3 times ULN and TBIL > 2 times ULN                                                            |
|                                 | ALT or AST $\geq$ 3 times ULN and International Normalized Ratio (INR) $\geq$ 1.5                               |
|                                 | ALT or AST $\geq$ 3 times ULN with fatigue, nausea, vomiting, right upper quadrant pain/tenderness, fever, rash |
|                                 | ALP > 3X ULN                                                                                                    |
|                                 | ALP $\geq$ 2.5 X ULN and TBIL > 2X ULN                                                                          |
|                                 | ALP $\geq$ 2.5 times ULN with fatigue, nausea, vomiting, right upper quadrant pain/tenderness, fever, rash      |
| ALT/AST $\geq$ 1.5 and < 2X ULN | ALT or AST $\geq$ 4 times baseline level                                                                        |
|                                 | ALT or AST $\geq$ 3 times baseline level for more than 2 weeks                                                  |
|                                 | ALT or AST $\geq$ 2 times baseline and TBIL > 2 times ULN                                                       |
|                                 | ALT or AST $\geq$ 2 times baseline level and international normalized ratio (INR) $\geq$ 1.5                    |

| Baseline | Treatment Period                                                                                                     |
|----------|----------------------------------------------------------------------------------------------------------------------|
|          | ALT or AST $\geq 2$ times baseline with fatigue, nausea, vomiting, right upper quadrant pain/tenderness, fever, rash |

- 2) CK value > 5 times ULN;
- 3) Blood lipase and/or amylase  $\geq 3$  times ULN. Refer to Annex 1 for subsequent monitoring and treatment procedures;
- 4) The subject experienced a severe hypoglycemic event (Grade 3, refer to Section 7.7. 2);
- 5) Persistent Grade 1 or 2 hypoglycaemic events (persistent hypoglycaemia is defined as at least 1 hypoglycaemic event per day for  $\geq 2$  days).

#### 4.5.3 Withdrawal Criteria

Including subject withdrawal on his own initiative and subject withdrawal at the discretion of the investigator:

- 1) The investigator considers that the subject should not continue to participate in the trial if the adverse event that the investigator considers is necessary to stop the treatment occurs (for gastrointestinal adverse reactions, it is considered to be related to drug effect, and it is recommended that the investigator may consider that the subject withdraws from the study if severe adverse reactions still exist after dose adjustment in combination with specific clinical conditions);
- 2) If pancreatitis is confirmed by clinical symptoms or imaging examination, the trial will be terminated immediately;
- 3) Subjects who have poor compliance, no longer receive medication or tests before completing all the trials, and cannot insist on completing the trial as planned, including subjects who are unable to control diet well, fail to take medication as prescribed, or have other factors that may affect the efficacy observation;
- 4) Participants in other clinical trials during the trial, and participation in other trials is defined as signing the informed consent form for other trials;
- 5) Withdrawal of informed consent by the subject;
- 6) Unblinding due to various reasons;
- 7) Female subject is pregnant;
- 8) The investigator considers that it is not suitable to continue to participate in this clinical trial.

#### **4.5.4 Exit Procedure**

If a subject decides to withdraw from the trial, an early withdrawal visit should be performed and then withdrawn from the study. Whenever possible, subjects were to return to the study site for an early withdrawal visit. The date of the subject's last injection of study drug and the reason for withdrawal were recorded in the eCRF.

#### **4.6 Subject Withdrawal from the Study**

If a subject discontinues study treatment and voluntarily withdraws consent for follow-up data collection, data collection should not continue; However, subjects who discontinue study drug but do not withdraw consent may continue to participate in study follow-up for safety/efficacy assessments.

### **5 Study Drug and Other Treatments**

#### **5.1 Treatment Assignment**

##### **5.1.1 Subject Number and Treatment Assignment**

After signing the informed consent form, the subject will be given the subject number, and then the screening examination will be performed. If the screening is successful, the subject will be randomly assigned to five treatment groups of Cohort 1, Cohort 2, Cohort 3, Cohort 4 and Cohort 5, with investigational drug: placebo = 8: 4 in each cohort group, with a total of 12 subjects.

##### **5.1.2 Randomization and Blinding**

Randomized double-blind trial in which subjects, investigators, data analysts, and all medical personnel involved in the treatment or clinical assessment will remain blinded to the true status of the treatment from the time of randomization until the database is locked, using the following methods:

Different drug numbers correspond to random numbers in the centralized randomization system, and the blind codes of drug numbers and random numbers remain unknown to the subjects and investigators throughout the trial. The random list shall be kept by a specially-assigned person.

The investigational drug and placebo will use exactly the same packaging, labeling, administration time, appearance, taste and smell to conceal the true situation of the treatment drug.

Unblinding was to be performed only in the event of an emergency for a subject and at the end of the study.

Unblinded Sponsor personnel will not be blinded during the course of this study.

## 5.2 Study drug

### 5.2.1 Physical and chemical characteristics of the study drug

|                   |                                                                                                                                                                            |
|-------------------|----------------------------------------------------------------------------------------------------------------------------------------------------------------------------|
| Molecular Weight: | 4560.32 Daltons                                                                                                                                                            |
| Description:      | White to off-white powder                                                                                                                                                  |
| PI:               | 5.2                                                                                                                                                                        |
| Solubility:       | Solvent: 20 mM Tris buffer at pH 8.0 and 150 mM sodium chloride.
Solubility: Not less than 10 mg/mL at 25 °C.
Solubility Description: Sparingly or slightly soluble. |

### 5.2.2 Study Drug Strength and Manufacturer

The IBI362 drug product is IBI362 for injection and consists of 2 mg IBI362 and the inactive ingredients tris (hydroxymethyl) aminomethane, mannitol and sucrose. The vial contents are reconstituted with sterile water for injection to obtain a clear solution of IBI362.

"The placebo is an IBI362 mimetic, and the placebo consists of the inactive ingredients tris (hydroxymethyl) aminomethane, mannitol, and sucrose." The vial contents are reconstituted with sterile water for injection to obtain a clear solution devoid of active ingredients.

The drug product strength used in this study was 2 mg/vial, and the placebo strength matched the drug product and was provided by the Sponsor.

### 5.2.3 Storage

The drug product and placebo should be stored under refrigerated conditions (2 °C to 8 °C).

### 5.2.4 Mode of administration

Both IBI362 and placebo will be administered by subcutaneous injection once a week. Each dose should be prepared and injected by the study nurse. See the Instructions for Use for details of the preparation and use of the study drug.

## 5.3 Concomitant Therapy

### 5.3.1 Prohibited Medications

The following medications and measures are contraindicated:

1. Growth hormone and its analogues;
2. Any systemic corticosteroid (including intravenous, oral, intra-articular) administered for  $\geq 7$  days. Corticosteroid hormone: Mainly for glucocorticoid hormone, including short-acting: hydrocortisone, cortisone; Intermediate effect: prednisone, prednisolone, methylprednisone, triamcinolone; Long-acting:

dexamethasone, betamethasone, etc.;

3. Drugs for weight control, such as sibutramine hydrochloride, orlistat, phentermine, phenylpropanolamine, chlorpheniramine, phentermine, bupropion, lorcaserin, phentermine/topiramate mixture, naltrexone/bupropion mixture and some health products with "weight loss" indications;
4. Drugs that have an effect on body weight: tricyclic antidepressants, drugs for psychiatric disorders and neuroleptics such as imipramine, amitriptyline, mirtazapine, paroxetine, phenelzine, chlorpromazine, thioridazine, clozapine, olanzapine, valproic acid, valproic acid derivatives, lithium salts; Antidiabetic agents: metformin, SGLT2 inhibitors, and other agents that can cause weight gain or loss.
5. Any drug or herbal medicine known to have common toxic effects on major organs, or any drug that may interfere with the interpretation of efficacy and safety data.

#### **5.4 Dosing during pregnancy, childbearing potential, or lactation**

##### **5.4.1 Pregnancy**

Pregnant women should not be enrolled in this study and contraception is required during the trial.

##### **5.4.2 Childbearing age**

Female subjects of childbearing potential who are sexually active with a non-sterilized male partner, and non-sterile male subjects who are sexually active with a female partner of childbearing potential must use at least 1 acceptable effective method of contraception from screening until 8 weeks after the last dose and should discuss the discontinuation of contraception with a responsible physician after that time point.

Women were considered postmenopausal after 12 months of menopause without an alternative medical cause. The requirements according to age are as follows:

- Women  $\geq 50$  years of age are considered postmenopausal if they have been amenorrheic for 12 months or more after cessation of exogenous hormone therapy and their luteinizing hormone and follicle-stimulating hormone levels are in the accepted postmenopausal range.
- Women  $< 50$  years of age were considered postmenopausal if they had been amenorrheic for 12 months or more after cessation of all exogenous hormonal therapy, had been oophorectomized with the last menses occurring  $> 1$  year earlier with radiation therapy, had been amenorrheic with the last menses occurring  $> 1$  year earlier with chemotherapy, or had been surgically sterilized (bilateral oophorectomy or hysterectomy).

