10. 212-lead electrocardiogram (ECG) parameters include: RR interval, PR interval, heart rate (HR), QT interval, QTcF (refer to Appendix 3 for calculation formula). Time points of examination: 1W: screening period, within 1h before the first administration, 12h after administration, 24h after administration (D2), 48h after administration (D3), 72h after administration (D4); 2W: within 1h before the second administration; 3W: within 1h before the third administration; 4W: within 1h before the 4th administration and 24h after administration (D23); 5W: within 1h before the 5th administration and 24h after administration (D30); 6W: within 1h before the 6th administration; 7W: within 1h before the 7th administration; 8W: within 1h before and 24h after the 8th administration (D51); 9W: within 1h before the 9th administration and 24h after administration (D58); 10W: within 1h before the 10th administration; 11W: within 1h before the 11th administration; 12W: within 1h before the 12th administration, 24h (D79) and 48h (D80) after administration; 168h after the last dose (D85), at the last follow-up visit (D134). If the subject has abnormal ECG, the investigator can perform additional ECG according to the actual situation. The window period for ECG examination at each visit refers to the window period for PK sampling at the same time point.
11. Serological detection of infectious diseases: including Human Immunodeficiency Virus (HIV) antibody, hepatitis B virus (HBV), hepatitis C virus (HCV) antibody and syphilis antibody.
12. [5.4.2](#)Blood pregnancy test for women of childbearing potential (refer to Section 5.4. 2 for the definition of childbearing potential)
13. Thyroid function indicators include: Thyroid Stimulating Hormone (TSH), free triiodothyronine (Free Triiodothyronine, FT3) and free thyroxine (Free Thyroxine, FT4).
14. Glycosylated hemoglobin test in central laboratory: blood collection points are at V2 visit (D1) and V20 visit (D85) and unscheduled. 2 mL of whole blood will be collected at each blood collection point. Refer to the central laboratory manual for detailed operation procedures.

15. 4For subjects with fasting blood glucose of 6.1-7.0 mmol/L at screening, venous blood glucose 2 hours after OGTT glucose load should be collected for confirmation. Refer to Appendix 5 for OGTT method.

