#### **6.2.6 Pregnancy test**

A blood pregnancy test is required for women of childbearing potential before enrollment. If the pregnancy test is positive, the subject is not eligible/must be discontinued from the study. If pregnancy is suspected during the study, it should be repeated.

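### Section 5.4.2 asks for weaker evidence of postmenopausal status in women under 50 than in women of 50 and over, and pregnancy testing and contraception depend on it

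*Protocol*

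**What the plan says.** Section 5.4.2 opens with a condition that covers every age: "Women were considered postmenopausal after 12 months of menopause without an alternative medical cause". It then gives requirements by age.

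- **50 and over:** at least 12 months of amenorrhoea after exogenous hormones are stopped, "and their luteinizing hormone and follicle-stimulating hormone levels are in the accepted postmenopausal range".
- **Under 50:** a list of alternatives. The first is "years of age were considered postmenopausal if they had been amenorrheic for 12 months or more after cessation of all exogenous hormonal therapy". Routes through radiation and chemotherapy follow, and the list ends "or had been surgically sterilized (bilateral oophorectomy or hysterectomy".

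Other parts of the protocol rely on this section. The note on the pregnancy-test row (note 12 to Table 2, note 11 to Tables 4 and 6) reads "Blood pregnancy test for women of childbearing potential (refer to Section 5.4. 2 for the definition of childbearing potential". Section 6.2.6 says "A blood pregnancy test is required for women of childbearing potential before enrollment". The contraception duty in 5.4.2 is addressed to "Female subjects of childbearing potential who are sexually active with a non-sterilized male partner", with a parallel duty for men. Exclusion criterion 7 and section 4.3 tie contraception to childbearing potential as well.

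**The concern.** The two age rules are not equally strict, and the lighter one falls on the group in which continuing fertility is harder to rule out. A definition of this kind exists to keep a woman who could be pregnant, or become pregnant, from being dosed untested and without contraception. If the rule is looser for younger women, a site that follows the protocol exactly can leave such a woman outside both protections. Eligible ages run from 18 to 75, so both rules will be used.

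Two related gaps concern women of 50 and over. Their rule needs hormone values that the protocol does not schedule, and the surgical, radiation and chemotherapy routes are not offered to them.

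**Working it through.** No arithmetic decides this point. The check compares the two rules and then traces what depends on them.

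**Step 1: the logic of the two rules.**

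| | Under 50 | 50 and over |
|---|---|---|
| Lead-in: no alternative medical cause | applies | applies |
| At least 12 months of amenorrhoea off hormones | sufficient alone (first item of an 'or' list) | necessary |
| LH and FSH in postmenopausal range | not asked | also necessary ('and') |
| Surgical, radiation, chemotherapy routes | listed | not listed |

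Take two women with the same findings: 12 months of amenorrhoea off hormones, no other cause identified, LH and FSH below the postmenopausal range. Under 50, she meets her rule. At 50 or over, she does not. The amenorrhoea route is strictly weaker for the younger woman.

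**Step 2: can the hormone condition be applied from trial data?** LH and FSH appear neither in the schedules (Tables 2, 4 and 6) nor in the routine laboratory list (Table 14), where the hormones are FT3, FT4, TSH and calcitonin. A site would need an existing or unscheduled result.

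**Step 3: what depends on the classification.** The schedule notes send the reader to 5.4.2 for the meaning of childbearing potential. The only status rules in that section are the postmenopausal ones, so they settle who is tested.

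- Cohort 4 (Table 4): screening, D29, D57, D85 and D113, which is 5 scheduled tests.
- Cohort 5 (Table 6): screening, D29, D57 and D85, which is 4 scheduled tests.
- In addition: reconfirmation within 5 days before dosing if screening was more than 5 days earlier (note 1), and a test at early withdrawal.

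**Step 4: length of the contraception duty.** It runs from screening, at the earliest D-21, to 8 weeks (56 days) after the last dose.

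- Cohort 4: last dose D106, and 106 + 56 = D162. From D-21 this is 182 days, and 182 / 7 = 26 weeks.
- Cohort 5: last dose D78, and 78 + 56 = D134. From D-21 this is 154 days, and 154 / 7 = 22 weeks.

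These are maxima, because screening may start later than D-21 and the duty binds only women sexually active with a non-sterilised male partner.

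**The case against.** The strongest reply is that the lead-in governs both age groups. A reader might infer that a young obese woman whose periods have stopped because of anovulation is classed as postmenopausal. The text does not support that: anovulation is an alternative medical cause, and once it is recognised she does not qualify. What remains is narrower. For women under 50 no test supports the judgement that no other cause exists, while for older women one is demanded.

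A reader might also infer that women under 50 escape testing and contraception altogether. That goes too far. Section 5.4.1 says without qualification that contraception is required, section 6.2.6 calls for a repeat test when pregnancy is suspected, and exclusion 7 bars any pregnant woman. Note 1 also names the pregnancy test without limiting it. These safeguards are partial. Sections 4.3 and 5.4.2 narrow the contraception duty to childbearing potential, testing on suspicion is reactive, exclusion 7 works only if the pregnancy is known, and the note on the test row restricts who is tested. The accurate statement is that the test is not required.

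A third inference is that the two age limits were transposed by mistake. No part of the protocol states the opposite rule, so this cannot be shown. The documents show only the asymmetry.

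Finally, the gaps for women of 50 and over err on the safe side: a woman who cannot be classified stays in the tested group. That is correct. Table 14 is also a list of routine tests, and nothing forbids an unscheduled assay. These gaps are reasons to tidy the section and are not hazards in themselves.

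**Conclusion.** The point holds as a defect of definition. Section 5.4.2 asks less evidence of women under 50 than of older women, and the required pregnancy tests, the contraception part of exclusion 7 and the contraception duty all follow from it. A woman under 50 who meets the amenorrhoea item but may still be fertile has no required test out of 5 (Cohort 4) or 4 (Cohort 5), and no duty under 5.4.2 for up to 26 or 22 weeks.

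This rests on two assumptions: that sites apply the age rules as written, and that a year of amenorrhoea is no surer a sign of menopause under 50 than above it. The protocol does not state the second.

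The number of women concerned is not given and is probably small. Cohorts 1 to 3 (36 participants) are already enrolled, which leaves 24 planned participants of both sexes in Cohorts 4 and 5. Sample size, endpoints and analyses are untouched. The case for acting is participant safety at low cost.

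**What to change.** The sponsor should reconcile the two age rules in 5.4.2 with each other, with the lead-in sentence, with the general contraception sentence in 5.4.1 and with the laboratory schedule. The result should be that the evidence required of the younger group is not weaker than that required of the older group. The section should also state to which ages the surgical, radiation and chemotherapy routes apply. If hormone levels stay part of the definition, the schedule should say when they are measured or which existing results are accepted. The criterion itself is for the sponsor to set.

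The cost is wording in one section, perhaps with a line in the schedule notes. In practice it may mean a few extra pregnancy tests, an assay already scheduled, or an occasional hormone assay.
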